### **Data collection using mHealth technology**

We will develop three mHealth applications to support the CLIP trial. The first will be used in all countries and the second and third will be used in Nigeria, Mozambique and Pakistan during the definitive trial phase.

The first application will be mobile phone-based while the other two will use a tablet-based device.

For intervention clusters only, the first mHealth application is the CLIP POM (described in detail, previously). This will be used to collect routine antenatal visit data and miniPIERS variables. These data will be entered into an integrated decision guide to give real-time advice to cHCPs in terms of appropriate patient management and decisions for interventions (e.g., appropriateness and timing of transport to CEmOC facility, and community initiation of antihypertensive and MgSO4 therapy, as discussed above). Women will be identified both by demographics information and by unique surveillance IDs to enhance identification through the system.

For both intervention and control clusters, the second mHealth application will be a tablet device used by the field team for routine data collection during household surveys (see above). In this way, survey data will be automatically synchronised with a centralised data warehouse, and collected efficiently (given no double handling of paper forms and efficient enforcement of complete data entry). GPS co-ordinates will be provided in real-time to confirm the place and time of each survey event.

For both intervention and control clusters, the third mHealth application will be a tablet device used by an independent team of skilled interviewers who will conduct a detailed verbal and social autopsy / morbidity review when the quarterly surveys reveal the occurrence of an adverse maternal and/or perinatal event (death or major morbidity). The application will be adapted from that developed by the WHO.

Each CLIP site will participate in the design and development of mHealth tools and will conduct usability testing of the final application prototypes before the trial begins in order to ensure acceptability and usability of the tools by users (cHCPs and surveillance teams). Post-trial evaluation of health worker and stakeholder perspectives on the acceptability and usability of the mHealth tools will be performed.

Data on individual women entered into all mHealth applications will be linked using a unique identifier code. This code will be provided to each woman after they consent for the trial on a study ID card. The key for these unique identifiers will be developed after the baseline survey by the Data Manager in each country and will not be shared with the Trial Coordinating Centre at UBC, ensuring privacy and confidentiality of the women is maintained at all times.

Patient data security is at all times of utmost importance, and will thus be maintained throughout mHealth system operations.

- Valid usernames and passwords will be used to limit unauthorized access to device data as well as access to the database and central document archives. The relevant password rules and encryption protocols will be applied.
- Encryption of data is required for any form of storage or transmission between devices and systems.
- Data validation will be performed at every stage of data input as well as on all data access requests to minimize false scripting.

In addition, all safety regulations pertaining to medical diagnostic and monitoring tools will be upheld. Any interfaces between patient, device and user will have the necessary protection systems to ensure the safety of the patient and operator.

## **2.11 SAMPLE SIZE CALCULATIONS**

Each country is independently powered to assess the chosen primary outcome. The data upon which the estimates have been made are routinely at the conservative end of the published or available range, and were generally provided by the site investigators. However, these calculations will be revisited once the CLIP Feasibility Study maternal and perinatal morbidity and mortality data are in hand. We have planned an individual patient data (IPD) meta-analysis at the completion of each of the individual country trials to

ensure adequate power for an analysis of maternal mortality and morbidity.

**Table 3** Sample size calculations (Mozambique to be determined)

| Country                                                                         | Nigeria            | Mozambique         | Pakistan      | India               |
|---------------------------------------------------------------------------------|--------------------|--------------------|---------------|---------------------|
| Unit of randomization                                                           | LGA                | AP                 | Union Council | PHC                 |
| Population per unit of randomization                                            | 70,000             | 25,000             | 32,000        | 27,000              |
| Annual birth rate (/1000/yr)                                                    | 16                 | 40                 | 14            | 22                  |
| Births/2yr                                                                      | 2240               | 2000               | 900           | 1200                |
| MMR (/100,000 live births)                                                      | 800                | 388                | 267           | 150                 |
| Intra-cluster co-efficient                                                      | 0.006 † | 0.002 ‡ | 0.002*        | 0.001**             |
| Incidence of maternal & perinatal/neonatal M&M                                  |                    |                    |               |                     |
| control clusters                                                                | 28.8%              | 14.0%              | 9.6%          | 5.4%                |
| intervention clusters                                                           | 23.0%              | 11.1%              | 7.7%          | 4.3%                |
| Number of clusters (total)                                                      | 10                 | 12                 | 20            | 12                  |
| Number of births in Definitive CLIP Trial (2 years)                             | 22,400             | 24,405             | 18,000        | 13,000              |
| Additional births from Pilot CLIP Trial (4 clusters/1 year)                     | 4480               | n/a                | 1800          | 2400                |
| Total number of births (Pilot & Definitive Trials)                              | 26,880             | 24,405             | 19,800        | 19,200              |
| Expected referrals at month 6 of Pilot Trial assuming 5% incidence of HDP       | 112 [92, 132]      | 100 [81, 119]      | 45 [32, 58]   | 60 [45, 75]         |
| Number of women to be referred at month 6 of Pilot Trial to meet 50% use target | 56                 | 50                 | 23            | 30                  |
| Number of health facilities (total)                                             |                    |                    |               |                     |
| PHC/RHC                                                                         | 120                | 44                 | 42            | 22                  |
| EmOC                                                                            | 10                 | 10                 |               | 22                  |
| Number of CHCPs (total)                                                         | 250 CHEWs & 45 HAs | 170                | 400 LHWs      | 60 ANMs & 360 ASHAs |

ANM: assistant nurse midwife; AM: Administrative Posts; ASHA: accredited social health activist; CHEW: community health extension worker; CHCPs: community health care providers; CHW: community health worker; EmOC, emergency obstetric care; LGA: Local Government Area; LHW: Lady Health Worker; M&M: morbidity and mortality; MMR: maternal mortality ratio; PHC: Primary Health Centre; RHC, rural health centre.

\* calculated from Sindhi miniPIERS facility data. † assumes 3-fold increase in ICC over Sindh; ‡ assumes same ICC as Sindh (urban population in Maputo); \*\* assumes half the ICC of Sindh. In these calculations, we have used risks at the lower end of the published ranges for that risk and milieu.

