## SECTION 2: THE CLIP TRIAL

### 2.1 THE CLIP TRIAL DESIGN

We have designed a two-phased community (including PHC-level) cRCT encompassing both rural and urban settings to be fully powered in each of:

- Ogun State, Nigeria
- Maputo and Gaza Province, Mozambique
- Hyderabad and Matiar districts in Sindh Province, Pakistan.
- Belgaum and Bagalkot districts in Karnataka State, India

The trial will be phased from the Pilot CLIP trial to Definitive CLIP trial on the basis of a satisfactory rate of use ( $\geq 50\%$ ) of the CLIP 'package of care' in appropriate women in all countries but Mozambique (see section 2.2 intervention for details on the 'package of care'). Mozambique will be unique in that they will rely on an extended period of feasibility to pilot test all Trial systems and tools before directly beginning a definitive trial. Foregoing the Pilot in Mozambique was felt to be appropriate based on their experience with community-based surveillance and will ensure timelines of the trial are met within a manageable budget.

For all other countries, use of the package in the Pilot phase will be defined as appropriate referral (urgent or non-urgent) to a facility able to provide comprehensive emergency obstetric care (CEmOC) in appropriate women during the first six months of the Pilot CLIP trial (Figure 2). This accelerated transition from Pilot CLIP trials to Definitive CLIP trials will: (i) save resources in the long term as the research infrastructure will be maintained in all countries and, thereby, start-up costs will be reduced as will core infrastructure costs at UBC, and (ii) deliver more rapidly the primary CLIP research question, does the CLIP community intervention improve outcomes for mothers and babies?

Full details of the sample size calculation for both Pilot and Definitive trial phases can be found in Table 3.

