#### **For CLIP Pilot and Definitive trials**

**Control clusters** Women receive the current pattern of care

**Intervention clusters** Women and their communities receive the CLIP intervention

The primary implementers of the CLIP intervention will be cHCPs, the nature of whom will differ between countries. In Nigeria, these are Community Health Extension Workers (CHEWs) and Health Assistants (HAs); in Mozambique, these are Agente Polivalente Elementares (APEs); in Pakistan, these are Lady

Health Workers (LHWs); and in India, these are Accredited Social Health Advocates (ASHAs) and Auxiliary Nurse Midwives (ANMs). Unless context-specific, we will use the term cHCP to describe these cadres of health providers for simplicity. The training and experience of these groups are described in Table 2.

As the primary outcome changes between the Pilot and Definitive Trials, the women in the Pilot Trials will contribute to the sample size of the Definitive Trials. We plan that each pair of Pilot and Definitive CLIP Trials will span 48 months (36 months' recruitment) as shown in Figure 7 below. In India, the Pilot phase

[figure not shown]

will be shorter due to the difference in surveillance process as described later in this protocol.

**Figure 7:** CLIP trial timeline

cHCP community health care provider, cRCT cluster randomised controlled trial, mHealth mobile health

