To ensure reasonable balance between the two groups, we will use restricted, stratified randomisation to allocate clusters to the intervention and control groups. We will be using only one continuous stratification variable for the randomization of clusters in each country. For all countries this will be Population size. The randomization algorithm ensures adequate balance on the stratification variable over the Intervention arm and the Control arm. Allocations that fail any of the balance criteria will be excluded, and only allocations that meet all criteria are eligible for consideration. The final allocation scheme is a random selection from the list of eligible allocations.

The current algorithm is implemented using R Programming and can consider the following balance criteria:

1. Means ratios: the mean value over intervention clusters and the mean value over control clusters have a ratio no less than 0.9 and no greater than 1.1 (10%).
2. Mean relative to overall mean: the overall mean is the mean over all clusters; mean value in each arm is within 10% of overall mean.
3. Absolute difference in sums: the absolute difference between sums in the two arms is within 10,000.
4. Wilcoxin rank sum: Allocations where the Wilcoxin rank sum test have p-value <0.01 will be excluded.

5. Kolmogorov-smirnov test: Allocations where the Kolmogorov-smirnov test have p-value  $<0.01$  will be excluded.

In the pilot phase of the trial we randomize 4 clusters per country, except Mozambique where no Pilot phase is occurring. When we approach the definitive phase of the trial, these 4 clusters will be included in the randomization algorithm together with the new clusters, and their previous allocations will serve as an additional requirement for the algorithm. The set of eligible allocations will be those that meet the list of balance criteria and the pilot-allocation requirement.

We may or may not use all of the balance criteria listed, and the cut-points listed may be modified. These are common criteria and cut-points used in the literature, but adjustments may be needed if the resulting number of eligible allocations is deemed inadequate.

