## 2.9 OUTCOMES

### • **Pilot CLIP Trials**

The **primary outcome** for the Pilot CLIP Trials will be common for all participating countries, and will be appropriate use of the CLIP package of care (methyldopa and/or MgSO4 and urgent/non-urgent transport to CEmOC facility) in women with the appropriate CLIP trigger. To justify continuing on with the Definitive CLIP Trial, by 8 months into the 12 month Pilot (with the exception of India where assessment will occur at 6 months), at least 50% of eligible women (i.e., with a trigger) should have received the package of care.

The Pilot CLIP Trials will recruit for 12 months, primarily to field test: application of the CLIP intervention, data collection, and research infrastructure through four quarterly surveillance cycles (in Pakistan).

The **secondary outcomes** for the Pilot CLIP Trials will be the adverse maternal and perinatal outcomes described below for the Definitive CLIP Trials.

The **other outcomes** will be the secondary and other outcomes described below for the Definitive CLIP Trials.

As the primary outcome will change between the Pilot and Definitive CLIP Trials, women recruited to the Pilot Trial will be included in the total sample analysed for the Definitive Trial.

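### Table 3's month-6 pilot referral counts are built on all four pilot clusters, although only intervention clusters can use the package, and the progression criterion has two definitions and two dates

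*Protocol*

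**What the plan says.** Table 3 in section 2.11 has two rows on the pilot. The first, "Expected referrals at month 6 of Pilot Trial assuming 5% incidence of HDP", prints 112 [92, 132] for Nigeria, 100 [81, 119] for Mozambique, 45 [32, 58] for Pakistan and 60 [45, 75] for India. The second, "Number of women to be referred at month 6 of Pilot Trial to meet 50% use target", prints 56, 50, 23 and 30.

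Section 2.4 says "In the pilot phase of the trial we randomize 4 clusters per country", with Mozambique excepted because it has no pilot. For control clusters, section 2.1 says "Women receive the current pattern of care". Under contamination bias, section 2.5 adds that control-cluster health workers have neither the mHealth tools nor the intervention package. Section 2.10 confines the CLIP POM application to intervention clusters, and section 2.1 makes POM the means of monitoring use during the pilot.

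The criterion is described twice. In section 2.1, "use of the package in the Pilot phase will be defined as appropriate referral (urgent or non-urgent") to a comprehensive emergency obstetric care facility during the first six months. Re-assessment follows at 7, 8 and 9 months if use is below 50% but climbing. In section 2.9, the pilot primary outcome names methyldopa and/or magnesium sulphate together with transport, and at least 50% of women with a trigger should have received the package "by 8 months into the 12 month Pilot (with the exception of India where assessment will occur at 6 months").

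**The concern.** A count meant to show 50% use should be half of the women in whom use is possible. Control-cluster women cannot receive the package, and without POM they cannot be recorded as having a trigger, so they belong in neither numerator nor denominator. Table 3 appears to include them.

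Two things are at stake. First, Table 3 is the only place where the criterion is turned into a number of women. A planner reading it would expect about twice as many eligible women as the pilot can supply, and so a more precise estimate of use than it will give. Second, because sections 2.1 and 2.9 differ on what use is and when it is judged, the same data could satisfy one and not the other. A woman who is referred without a drug indicated for her trigger counts as use under section 2.1, but arguably not under section 2.9.

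**Working it through.** **Inputs**
- Births per cluster over two years, Table 3, in the order Nigeria, Mozambique, Pakistan, India: "2240 | 2000 | 900 | 1200". Dividing by 4 gives 560, 500, 225 and 300 per cluster per six months.
- Incidence: 5% of births, from the row label.
- Pilot clusters: four per country, both arms together (section 2.4).
- Pilot split: **assumed 2:2**. The readable text gives no ratio, and Figure 10 is not shown. The definitive trial is 1:1 in every country, and pilot clusters keep their arm.

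**Step 1: reproduce the printed rows.** Births n = clusters × births per six months; expected = 0.05 × n; interval = expected ± 1.96 × √(n × 0.05 × 0.95).

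| Country | n, 4 clusters | Expected | Interval | Half |
|---|---|---|---|---|
| Nigeria | 2,240 | 112 | 91.8 to 132.2 | 56 |
| Mozambique | 2,000 | 100 | 80.9 to 119.1 | 50 |
| Pakistan | 900 | 45 | 32.2 to 57.8 | 22.5 |
| India | 1,200 | 60 | 45.2 to 74.8 | 30 |

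Every printed figure is recovered. Two clusters for 12 months, or one for 24, give the same totals, but neither fits the month-6 label or the six-month window in section 2.1.

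**Step 2: intervention clusters only (2:2), six months.**

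| Country | n, 2 clusters | Expected eligible | Interval | 50% count | Printed count ÷ expected |
|---|---|---|---|---|---|
| Nigeria | 1,120 | 56 | 42 to 70 | 28 | 56/56 = 100% |
| Pakistan | 450 | 22.5 | 13 to 32 | 12 (11.25 rounded up) | 23/22.5 = 102% |
| India | 600 | 30 | 20 to 40 | 15 | 30/30 = 100% |

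**Step 3: other splits.** With three intervention clusters the printed counts are 67%, 68% and 67% of the expected eligible women; with one they are 200%, 204% and 200%. At the table's own 5%, no split that includes a control cluster gives 50%.

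**Step 4: precision of the observed percentage.** Around 50% use, the 95% half-width is 1.96 × √(0.25/m), with m eligible women and clustering ignored.
- Nigeria: m = 112 gives 9 points; m = 56 gives 13.
- Pakistan: m = 45 gives 15 points; m = 22.5 gives 21.
- India: m = 60 gives 13 points; m = 30 gives 18.

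**Step 5: if the counts were the benchmark.** Let the number of users be binomial on n births in two clusters, with probability 0.05 × u, where u is true use. The chance of reaching the printed count is:

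| True use u | Nigeria (≥56 of 1,120) | Pakistan (≥23 of 450) | India (≥30 of 600) |
|---|---|---|---|
| 50% | 0.00014% | 0.12% | 0.03% |
| 75% | 2.0% | 8.6% | 7.1% |
| 90% | 22.8% | 29.6% | 30.3% |
| 100% | 51.9% | 48.7% | 52.6% |

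**Step 6: Mozambique.** The table prints 100 and 50 for a pilot that sections 2.1 and 2.4 say will not take place. The table's own row for additional pilot births shows n/a.

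**The case against.** The strongest reply is that the counts decide nothing. Wherever the protocol states the rule (sections 2.1 and 2.9) it is a percentage of appropriate or eligible women, and POM-based monitoring keeps control women out of the observed percentage. The gate is also not mechanical: low but climbing use leads to re-assessment, identifiable barriers lead to remedy and deferral, and decisions are taken with the sponsor after advice from the data safety monitoring board. All of this stands. A reader might infer that a country with excellent uptake would fail because it missed the printed count. The documents do not support that, since no passage holds a country to the count.

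A reader might also put the chance of reaching the count at 90% use at 0.9^56 = 0.3% in Nigeria or 0.9^30 = 4% in India. That fixes the number of eligible women at exactly its expectation. The number is random, as the intervals in Table 3 acknowledge, and the chances are those in step 5.

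It can further be said that a trigger is not the same as a hypertensive disorder. Triggers include absent fetal movements and vaginal bleeding, and if 10% of women had one (an assumption) the printed counts would be 50% to 51% of those eligible in two clusters. This stands as a caution about any fixed count, but the row states 5% hypertensive disorders as its basis. Finally, the rows may have been meant for two clusters over 12 months. In that case the month-6 labels are wrong, and the table still needs correction.

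**Conclusion.** The point holds in limited form and should be fixed. The two pilot rows of Table 3 count women in both arms. Under an assumed 2:2 split, the expected number of eligible women is overstated twofold and the printed 50% counts equal about 100% of those who could use the package. That figure depends on the split; that the counts are not 50% does not, given the table's 5% incidence and at least one control cluster.

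The practical effect is on planning and precision: the pilot percentage will rest on about half the women that the table suggests. The decision itself would be misdirected only if the counts were used as the benchmark, in which case a country with 90% true use would reach its count about 23% of the time in Nigeria and 30% in Pakistan and India.

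Separately, sections 2.1 and 2.9 contradict each other on the definition of use and the month of assessment. The month 7 to 9 re-assessments soften the timing difference but do not remove it, because they apply only below 50% and leave the definition untouched.

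**What to change.** - Recompute both rows on the intervention pilot clusters. Under 2:2, the expected numbers are 56 [42, 70] in Nigeria, 22.5 [13, 32] in Pakistan and 30 [20, 40] in India, with 50% counts of 28, 12 and 15.
- State the pilot allocation ratio in section 2.4, and enter n/a for Mozambique in both rows.
- Label the counts as planning figures, and say that the observed percentage of women with a trigger governs progression.
- Reconcile sections 2.1 and 2.9 so that the criterion has one definition of use and one assessment time per country. If the agreed time is not month 6, recompute the counts for it: at eight months with two clusters, Nigeria's expected number is 2 × 2,240 × 8/24 × 0.05 = 74.7, and half of it is 37.3.

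The cost is two table rows and a few sentences. The smaller counts will show wider uncertainty around the pilot decision. No data collection changes.
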